## **7 MONITORING OF SUBJECTS AND CRITERIA FOR WITHDRAWAL OF SUBJECTS**

### **7.1 Subject Discontinuation**

Therapy will be discontinued for the following reasons:

1. Major bleeding complication including intracerebral hemorrhage or stroke, GI hemorrhage, need for major surgery.
2. One episode of severe priapism defined as priapism lasting for more than 4 hours or requiring transfusion or surgical therapy (see Section 4.4.2.3 for further details of priapism monitoring)

3. Positive quantitative blood HCG or pregnancy
4. New retinal detachment, hemorrhage or clinically significant visual change (Subjects will be instructed by site personnel to alert their local CI of any visual changes between study visits; the CI will schedule an immediate evaluation by an ophthalmologist if a randomized subject complains of changes in vision.)
5. Serious adverse events considered to be related to the study drug
6. Introduction of specific treatments for pulmonary hypertension (excluding acute administration during a catheterization procedure to test vascular reactivity)
7. Initiation of chronic transfusion therapy (in this instance, EOS assessments should occur either immediately prior to initiation of transfusions or between 2-3 weeks after the transfusion)
8. Protease inhibitor treatment for HIV
9. If an emergency clinical unblinding of treatment assignment is required
10. Initiation of potent CYP3A4 inhibitor therapy (e.g., itraconazole, ritonavir, ketoconazole)

Sickle cell related clinical deterioration, other than those requiring initiation of chronic transfusion therapy, does not require withdrawal of study medication. Likewise, clinical deterioration of PH does not necessarily require discontinuation of study medication, unless the Investigator feels it is necessary to introduce another PH medication. In any situation where subject discontinuation is not required, the Investigator may always choose to discontinue the subject based on his or her clinical judgment. Any premature discontinuation of study drug precludes participation in the Open-Label Follow-up Phase of the MIT. At the time of study drug discontinuation all EOS visit assessments should be obtained to the extent possible. Such subjects should continue to be followed for adverse events and collection of other study data to the extent possible. Assessment of study endpoints should be made blinded to subjects' study treatment as much as possible.

## **7.2 Dose Modification or Discontinuation Due to Expected Adverse Events: Headache or Facial/skin Edema**

Dose adjustment instructions for symptomatic/dose limiting headache or facial/skin edema sufficient to warrant discontinuation of the drug (only for symptoms that are severe enough as described by subject or physician to warrant holding the drug) are provided herein.

1. If present during initial dose (20 mg) hold for one day and rechallenge, if symptoms occur upon rechallenge discontinue drug. Data collection should continue for such subjects to the extent possible.

2. If present during dose escalation (40 or 80 mg) hold drug for one day and restart at previously tolerated dose for one week. If symptoms recur, discontinue drug but continue to follow subject for collection of safety and other data. If tolerated for one week increase dose to desired level as dictated by protocol. If symptoms recur upon second increase hold drug for one day and drop dose to previously tolerated dose for the duration of the trial.

## **8 DESCRIPTION OF STUDY DRUG AND DOSING REGIMEN**

Sildenafil is an oral therapy for erectile dysfunction and is a selective inhibitor of cyclic guanosine monophosphate (cGMP)-specific phosphodiesterase type 5 (PDE5). It is available in tablet form (Pfizer). Pfizer will provide the drug and matching placebo for this study free of charge through an Independent Research Grant Agreement.

Potential AEs include hypotension, headache, flushing, dyspepsia, nasal congestion, urinary tract infection, abnormal vision, diarrhea, dizziness, rash, myalgia, epistaxis, insomnia, paresthesia, pyrexia, and decreased or loss of hearing.

During the randomized, double-blind phase, the initial dose of study drug (20 mg every 8H PO) is given for a total of 6 weeks, followed by 4 weeks of 40 mg TID, and finally 80 mg TID for 6 weeks. All study drug should be given by mouth.

The open label sildenafil will be available in two tablet strengths: 20 and 25mg. At the beginning of the open label phase, all eligible subjects will be down titrated from 80 mg TID of sildenafil or placebo to 20 or 25 mg of sildenafil TID. The doses will then be titrated upwards as tolerated. Doses will increase by 20-25 mg TID every 2 weeks. The maximum dose will either be 75 mg or 80 mg TID, depending on 20 mg or 25 mg tablet availability.

Refer to MOO Chapter 13.3 for additional taper guidance for patients who choose not to participate in the Open Label Follow-up Study upon completion of the MIT.

### **8.1 Packaging, Labeling, Blinding, Storage, and Return of Study Drug**

Pfizer will provide oral Revatio™ (sildenafil citrate) and matching Placebo (“Pfizer Product”) from multiple commercial batches, with differing expiration dates. Sildenafil citrate is a white to off-white crystalline powder with a solubility of 3.5 mg/mL in water and a molecular weight of 666.7. No additional dilution is required prior to administration. The product should be stored at controlled room temperature, 15° to 30°C (59°- 86° F). The study drug is stable through the date stamped on the product label and is administered orally.

All study drug (active and placebo) will be prepared by the central pharmacist at the Program Support Center, HHS Supply Service Center, [name], and shipped to participating sites’ pharmacies for dispensing. Study drug will be available in capsule formulation (over-encapsulated tablets). Placebo and active study drug capsules will

appear identical. The drug supply for the randomized double-blind phase will be packaged to allow the local site pharmacists to remain blinded to treatment group. Upon randomization of each subject, the Rho*RAND* system will send a randomization notification to the local pharmacist that provides the identification number of the bottle(s) (or kit) of study medication to be assigned/dispensed to that subject.

All unused study drug will be returned to the local pharmacy for disposal according to their standard operating procedures.

## **8.2 Subject Compliance**

Good subject compliance/adherence will be critical to the success of the study and will therefore be monitored in multiple ways. Subjects will be required to return their bottles of sildenafil or placebo at every scheduled clinic visit in order to receive their new supply of “treatment.” Each site will count the number of pills returned and compare to the expected number of pills returned in order to calculate percent compliance. In addition, subjects will be instructed to maintain a study drug log for one week in-between each visit during the double-blind phase. They will record if and when they took their daily doses of study medication. Subjects whose diary or pill count suggest <75% compliance will be counseled.

## **9 CLINICAL AND LABORATORY ASSESSMENTS**

### **9.1 Schedule of Study Events**

Table 3 and Table 4 list events and study assessments to be performed during the Screening Phase/Observational Follow-up Study and Main Interventional Trial, respectively.

**Table 3. Schedule of Events – Screening and Observational Follow-up Study**

|                                                                                                                                               | Screening      | Follow-up Study
(Every 6-12 months,
as possible) |
|-----------------------------------------------------------------------------------------------------------------------------------------------|----------------|--------------------------------------------------------|
| Sign Informed Consent                                                                                                                         | X              |                                                        |
| Medical history, physical examination, and vital signs (including weight)                                                                     | X              |                                                        |
| Standard laboratory tests (chemistry, CBC, urinalysis)                                                                                        | X              |                                                        |
| Hemoglobin Electrophoresis                                                                                                                    | X  |                                                        |
| HIV test                                                                                                                                      | X              |                                                        |
| Echocardiogram (TRV for RV systolic function)                                                                                                 | X              |                                                        |
| 6-minute walk test                                                                                                                            | X              |                                                        |
| Genotype studies                                                                                                                              | X              |                                                        |
| Pregnancy test                                                                                                                                | X              |                                                        |
| Biomarkers (Central Labs [RBC pellets], e.g. NT-BNP)                                                                                          | X              |                                                        |
| Adverse Events                                                                                                                    | X              |                                                        |
| Subject report of Hospitalizations/ED/Clinic visits                                                                                           |                | X                                                      |
| Subject report of Stroke / neurological events, surgical procedures, priapism, acute chest syndrome                                           |                | X                                                      |
| Subject report of hydroxyurea therapy, pulmonary hypertension therapy, iron chelation therapy, renal replacement therapy, transfusion therapy |                | X                                                      |

 Complete only for subjects who otherwise qualify for the MIT but for whom source documentation of hemoglobin electrophoresis is absent.

 AEs will be reported if they begin or worsen from the time a subject signs informed consent for the Screening Phase through 7 days after the last screening procedure and only if the investigator believes the event to be possibly associated with that study procedure.

**Table 4. Schedule of Events – Main Interventional Study**

|                                                                                                                                                                                                                                                            | Baseline       | Randomized, Double-blind Phase |                |                     | Open-Label Follow-up Phase  |
|------------------------------------------------------------------------------------------------------------------------------------------------------------------------------------------------------------------------------------------------------------|----------------|--------------------------------|----------------|---------------------|-----------------------------------------|
|                                                                                                                                                                                                                                                            |                | 6±1wk                          | 10±1wk         | 16± wk / early term |                                         |
| Sign Informed Consent                                                                                                                                                                                                                                      | X              |                                |                |                     |                                         |
| Interim medical history, physical examination, and vital signs                                                                                                                                                                                             | X              | X                              | X              | X                   |                                         |
| Standard laboratory tests (chemistry, CBC, urinalysis, including international normalized ration (INR) for subjects on vitamin K antagonist and activated partial thromboplastin time (aPTT) for subjects on therapeutic doses of unfractionated heparin ) | X              | X                              | X              | X                   |                                         |
| Echocardiogram (LV systolic/diastolic function)                                                                                                                                                                                                            | X  | X                              |                | X                   |                                         |
| Right heart catheterization – Hemodynamic parameters at rest                                                                                                                                                                                   | X              |                                |                | X                   |                                         |
| 6-minute walk test                                                                                                                                                                                                                                         | X  | X                              | X              | X                   |                                         |
| Borg dyspnea index                                                                                                                                                                                                                                         | X              | X                              | X              | X                   |                                         |
| NYHA/WHO functional class assessment                                                                                                                                                                                                                       | X              | X                              | X              | X                   |                                         |
| Pregnancy test                                                                                                                                                                                                                                             | X              | X                              | X              | X                   |                                         |
| Ophthalmologic Exam                                                                                                                                                                                                                                        | X  |                                |                |                     |                                         |
| Chest X-ray                                                                                                                                                                                                                                    | X              |                                |                |                     |                                         |
| O 2 saturation                                                                                                                                                                                                                                  | X              | X                              | X              | X                   |                                         |
| Quality of Life (SF-36 or Peds-QL)                                                                                                                                                                                                                         | X              |                                |                | X                   |                                         |
| Biomarkers (Central Labs, e.g. NT-BNP)                                                                                                                                                                                                                     | X              | X                              | X              | X                   |                                         |
| Symptoms documentation: hospitalizations, ED, Clinic, transfusions, ACS, priapism                                                                                                                                                                          | X              | X                              | X              | X                   |                                         |
| Prior/concomitant medications & narcotics                                                                                                                                                                                                                  | X              | X                              | X              | X                   |                                         |
| Compliance evaluations                                                                                                                                                                                                                                     |                | X                  | X  | X       |                                         |
| Pain Questionnaire (BPI)                                                                                                                                                                                                                                   | X              | X                  | X  | X       |                                         |
| Adverse Events                                                                                                                                                                                                                                             | X              | X                              | X              | X                   | X                           |

Confirmatory (may be the second echo that confirms the screening echo).Only for subjects enrolled in the trial with TRV ≥ 3.0 m/s.Confirmatory (<15% change from screening 6MW test distance).Subjects will maintain a diary for 1 week between each study visit. The diary will capture study drug compliance and self-reported pain assessments.Monitoring interval every 1-3 months, based on each site's standard practice.If obtained with 3 months of signing the main study consent document, this test need not be repeated.Patients who complete the treatment phase of the MIT but who choose not to participate in the Open-Label Follow-up Study will have study drug tapered for 3-7 days and return to the clinic for a safety follow-up visit approximately 30 days after completing MIT.Required for qualifying anti-coagulated patients and for those with no available record of an exam within the past year.Ophthalmologic exams will provide baseline information for clinicians.

## **9.2 Efficacy Evaluations**

### **9.2.1 Echocardiography**

Transthoracic echocardiography will be performed according to the guidelines of the American Society of Echocardiography. Transmitral flow, Doppler determinations of the severity of valvular regurgitation, and left ventricular stroke volume will be assessed and graded. Peak velocities of the E wave and A wave, the ratio of the E wave to the A wave, and the deceleration time will be measured. Isovolumic relaxation time will be measured as the time from aortic valve closure to the start of mitral inflow. See Appendix A for Echo checklist.

Tricuspid regurgitation will be assessed in the parasternal right ventricular inflow, parasternal short-axis, and apical four-chamber views, and a minimum of five sequential complexes will be recorded. Continuous-wave Doppler sampling of the peak regurgitant jet velocity will be used to estimate the right-ventricular-to-right-atrial systolic pressure gradient with the use of the modified Bernoulli equation ( $4 \times [\text{tricuspid regurgitant jet velocity}]^2$ ). Pulmonary-artery systolic pressure will be quantitated by adding the Bernoulli-derived pressure gradient to the estimated mean right atrial pressure.

The mean right atrial pressure will be calculated according to the degree of collapse of the inferior vena cava with inspiration: 5 mm Hg for a collapse of at least 50 percent and 15 mm Hg for a collapse of less than 50 percent.

During follow-up visits echocardiography should be performed on peak study medication dose i.e. 1-2 hours after study medication intake.

All echocardiograms will be completed at the local site and will be sent (either via FedEx or by posting to a secure website) to [name] echocardiogram central laboratory. All echocardiograms will be de-identified (removal of all of the patient's personal information) prior to them being sent for review and quality control. Refer to Chapter 4 of the walk-PHaSST Manual of Operations.

### **9.2.2 Right Heart Catheterization**

The pulmonary artery catheter is a triple lumen central venous catheter with two lumens devoted to the pressure transduction functions. The distal port will transduce pressure from the pulmonary artery and from the left atrium, when in the "wedge" position. The central venous port transduces right atrial pressures. During catheter placement, right ventricular pressures are transduced. Pulmonary artery systolic and diastolic pressures, right atrial pressure, pulmonary capillary wedge pressure, systemic artery systolic and diastolic pressures, cardiac output, and calculated systemic and pulmonary vascular resistances will be obtained using this methodology.

Baseline and endpoint RHC procedures should be conducted under similar conditions (e.g., level of sedation and oxygen). Endpoint RHC should be conducted at trough levels of study drug: approximately 4 hours post-dose.

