**Table 2. Inhaled NO and Oral Sildenafil Challenge at Baseline**

|        | Intervention     | Duration           | Assessment                 |
|--------|-------------------------|---------------------------|-----------------------------------|
| Step 1 | Baseline                |                           | Resting hemodynamics              |
| Step 2 | Inhaled NO 40 ppm       | 10 minutes                | Resting hemodynamics  |
| Step 3 | None                    | 10 minutes                | Resting hemodynamics              |
| Step 4 | Sildenafil 60 mg orally | 30 minutes post oral dose | Resting hemodynamics              |
| Step 5 |                         | 60 minutes post oral dose | Resting hemodynamics              |

 Resting hemodynamics assessed at the end of the 10 minute period of inhaled NO, while the subject is still inhaling the NO.

Right heart catheterization will be repeated at the end of the double-blind phase. This hemodynamic assessment will follow the guidelines below:

- Subjects will take their nighttime dose of study medication, but will not take their morning dose prior to right heart catheterization.
- Subjects will bring study medication to visit.
- Study medication is administered with direct observation by study coordinator
- Right heart catheterization will be performed approximately 4 hours after study medication is administered
- Baseline hemodynamic measurements will be performed as outlined in Table 2 (steps 1-3).
- Blinded study medication will be administered and hemodynamic measurements will be performed at 30 and 60 minutes post dosing as outlined in steps 4 and 5 of Table 2.

If during right heart catheterization, it is not possible to obtain an adequate reading of the pulmonary capillary wedge pressure, a left heart catheterization will be performed for the measurement of left ventricular end-diastolic pressure.

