- Emergency department visits, outpatient/day hospital visits and hospital admissions for sickle cell disease and those for complications of PH will be recorded
- Six-minute walk (with assessment of Borg dyspnea index, and NYHA/WHO functional class) 1-2 hours after taking the morning dose of study drug
- Echocardiogram with assessment of TRV LV and RV function 1-2 hours after taking the morning dose of study drug. All echocardiograms should be performed at least one hour after 6MW test. EXCEPTION NOTE: Echocardiogram will not be assessed at week  $10 \pm 1$
- Study drug compliance and daily pain assessment using the BPI --evaluated by subject for one week between each follow-up visit

End of the double-blind phase visit (week  $16 \pm 1$ ) will also include:

- In subjects with an initial study entry TRV  $\geq 3.0$  m/s a second right heart catheterization
- Quality of life assessment using SF-36 Quality of Life form (ages 14-adult) or Peds-QL (ages 12-13)

In subjects with TRV  $\geq 3.0$  m/s clinically indicated studies (according to accepted guidelines) for the work-up of subjects with pulmonary hypertension (PH) can be ordered at the discretion of treating clinicians. These studies could include:

- Collagen vascular screening tests (e.g., ANA, anti-centromere antibodies, anti SCL-70, antiphospholipid antibodies)
- Ventilation perfusion scan
- Chest X-ray (required for all MIT subjects at baseline), CT of chest
- Overnight pulse oximetry
- Spirometry with bronchodilation

- Lung volume
- Diffusing capacity for CO

Efficacy assessments will be done at peak dose (i.e., study medication should be taken 1-2 hours before measurements) when subjects are in a steady state.

A subset of clinical outcomes will be adjudicated by a blinded panel of experts. Adjudicated outcomes include: ACS, right heart failure, and clinical worsening.

Records of study drug used, dosages administered, and intervals between visits are kept during the study. Study drug accountability is performed on an ongoing basis by the study personnel and checked by the clinical research associate (CRA) during site visits and at the completion of the study. Subjects are asked to return all unused study drug at each visit.

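### The Week 16 right heart catheterisation is set about 4 hours after a dose, but that time is mislabelled as trough and sits beside unreconciled instructions on the morning dose, peak-dose timing and a further dose

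*Protocol*

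**What the plan says.** Protocol section 4.4.1 lists hemodynamic parameters first among the secondary efficacy endpoints. They are measured by right heart catheterisation (RHC) at baseline and Week 16 in subjects with TRV ≥ 3.0 m/s.

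The timing of the Week 16 procedure is spread over four places:

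- **Section 4.4.2.2, list after Table 2.** "Subjects will take their nighttime dose of study medication, but will not take their morning dose prior to right heart catheterization". Subjects bring their medication to the visit. Then: "Study medication is administered with direct observation by study coordinator", and "Right heart catheterization will be performed approximately 4 hours after study medication is administered". After steps 1-3 of Table 2: "Blinded study medication will be administered and hemodynamic measurements will be performed at 30 and 60 minutes post dosing".
- **Section 9.2.2.** "Endpoint RHC should be conducted at trough levels of study drug: approximately 4 hours post-dose".
- **Section 4.4.2.4.** "Efficacy assessments will be done at peak dose (i.e., study medication should be taken 1-2 hours before measurements". RHC is not exempted.
- **Section 8.** "the initial dose of study drug (20 mg every 8H PO) is given for a total of 6 weeks"; the later 40 mg and 80 mg steps are given three times daily.

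Table 2 specifies 60 mg of oral sildenafil at step 4 of the baseline challenge. Section 4.4.2.2 also refers to Appendix C for the challenge; its diagram is not reproduced in the text available here.

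**The concern.** The change in step 1 hemodynamics from baseline to Week 16 is the evidence for the secondary objective on hemodynamics after 16 weeks of therapy. What that change means depends on how long after a dose step 1 is taken. A value labelled trough will be read as the effect remaining at the end of a dosing interval. A value taken in mid-interval is the effect at that post-dose time, and may include some acute vasodilation. Reporting one under the name of the other would misdescribe the result.

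The conflicting instructions also leave site staff to work out three things for an invasive procedure: whether the withheld morning dose is the observed dose, whether the peak-dose sentence applies, and how many doses of study drug are given that day.

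**Working it through.** **1. Is 4 hours a trough?** Inputs: dosing every 8 hours (section 8, stated for the 20 mg step) and three times daily (section 8, for the 80 mg step in force at Week 16).

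- Mean interval = 24 h / 3 doses = 8 h, the same as the stated 8-hourly schedule.
- 4 h / 8 h = 50% of the interval.
- For 4 h to be the end of an interval, the regimen would need 24 / 4 = 6 doses a day, which appears nowhere.

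The trough label therefore cannot be reproduced from the protocol's own regimen. The nearest support is section 2.3, where the acute effect of a single oral dose peaks at 60 minutes and lasts up to 4 hours. That may explain the choice of 4 h, but it concerns effect, whereas section 9.2.2 speaks of drug levels.

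**2. The morning-dose instruction.** The section 4.4.2.2 list runs: night dose taken; morning dose not taken before RHC; medication brought in; dose given under observation; RHC about 4 h later. Read literally, the second item rules out a dose that the fourth and fifth require. They fit together if the morning dose is withheld at home and given at the clinic. That is the natural reading, but the text does not say so.

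**3. The peak rule.** Section 4.4.2.4 gives 1-2 h; sections 4.4.2.2 and 9.2.2 give about 4 h, which is outside that window. Hemodynamics are an efficacy endpoint by section 4.4.1, so on its wording the general sentence covers RHC. Section 4.4.2.4 does write out an exception elsewhere (no echocardiogram at Week 10), but none for RHC.

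**4. The further dose.** Time from the observed dose to step 4 = about 4 h + 10 min (step 2) + 10 min (step 3) = 4 h 20 min, plus the time taken for the measurements, so roughly 4.5 h. The regimen's interval is 8 h. Read literally, two study-drug doses fall about 4.5 h apart, and the protocol does not say how this fits the regimen or whether a regular dose is displaced.

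**5. Step 4 at the two visits.** Baseline: 60 mg of active drug for everyone (Table 2). Week 16: blinded study medication, which is placebo in one arm and in the other the subject's current dose, scheduled as 80 mg (section 4.4.2.4) or lower after adjustment (section 7.2). These are different tests.

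**6. Who is affected.** Section 11.6 plans about 33 subjects per arm and stratum, so 2 × 33 = 66 with RHC; section 6 requires at least 64.

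**The case against.** The strongest reply is that the protocol does state a time. Both RHC-specific sections give about 4 hours. Section 9.2 assigns timing test by test: 1-2 hours for the echocardiogram (9.2.1) and the walk test (9.2.3), about 4 hours for RHC (9.2.2). A specific rule normally overrides a general one, and bringing medication to an observed dose makes sense only if the morning dose moves to the clinic. All of this stands.

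A reader might infer more: that the endpoint has no defined timing, that step 1 could fall anywhere from 1-2 hours to 8-12 hours after a dose, or that sites will mix pre-dose and on-drug values. The documents do not support this. It would require sites to disregard two agreeing RHC instructions. Any estimate of drug remaining would need a half-life that the protocol does not give. A loss of power cannot be sized either, since section 11.6 gives 32 per group for pulmonary artery pressure without the effect size or standard deviation behind it.

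Nor is a comparison of the baseline and Week 16 oral challenges stated as an analysis. Section 4.4.2.2 only has acute effects assessed at both visits, and its reference to steps 4 and 5 can be read as borrowing just the 30- and 60-minute measurements.

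Three more points limit the concern. Appendix C may show the dose sequence. Both blinded arms follow the same schedule, so the randomised comparison can be interpreted as the effect at about 4 hours. The secondary tests are informal, with descriptive p-values (sections 11.2.2 and 11.5.3).

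What the reply does not remove is the wrong label, the literal conflict over the morning dose, the unexempted peak rule and the unexplained further dose.

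**Conclusion.** The concern holds as an inconsistency in operating instructions and a wrong label. The intended time is about 4 hours after a dose. Under 8-hourly or three-times-daily dosing that is half the interval, not a trough. The morning-dose instruction and the peak-dose sentence both conflict with it as written, and a second dose about 4.5 hours after the first is left unreconciled with the regimen.

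It touches one secondary endpoint in about 66 subjects. The primary walk-distance endpoint is unaffected. The trough finding needs only the dosing interval in section 8. The two-dose finding rests on a literal reading of section 4.4.2.2 and would lapse if Appendix C shows a different sequence. The correction is worth making because the procedure is invasive and the label would carry into the report of the result.

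**What to change.** Reconcile sections 4.4.2.2, 4.4.2.4, 8 and 9.2.2, together with Appendix C, on these points. This review does not choose the interval or the number of doses.

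- State one interval between the last dose and step 1, in the same terms everywhere, and say whether the observed dose is the withheld morning dose.
- State how many doses of study drug are given on the day of the Week 16 RHC and how they fit the regimen.
- Use trough only if the chosen time is the end of a dosing interval. Otherwise describe the hemodynamic change as measured at the stated post-dose time.
- Say whether the peak-dose sentence in section 4.4.2.4 applies to RHC.
- Record the clock time and dose level of the last dose before step 1. Sections 4.4.2.2 and 9.2.2 do not ask for the time; section 4.4.2.4 already keeps records of dosages administered.
- Report Week 16 steps 4-5 separately, as the response to blinded study medication at the subject's current dose, not as a repeat of the 60 mg baseline challenge.

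The cost is wording in the protocol and manual plus two data fields, with no added procedures or subjects. The one loss is that the two acute challenges can no longer be shown as a like-for-like pair.
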